### Statistical analyses

A statistical analysis plan will be written before the database is locked.

The population and clinical characteristics will be described (sex, age, family situation, cancer site).

The rate of QoL completion will be described for each questionnaire at each follow-up. QoL scores will be described at each follow-up.

Continuous variables will be described by means (standard deviation) and median (minimum-maximum). Qualitative variables will be described by frequencies and percentages.

#### Primary objective analyses

This study will respect the FDA psychometric validation methods [7].

The first objective is to validate translation of QUAL-E and MVQOLI by checking the psychometric properties.

1. Validity [32-34]: Face validity and content validity: The translated questionnaires will be analyzed by patients and experts to check that the items of the questionnaires are in line with to the original version (major domains treated, question ambiguity). This step was conducted by the '*Qualité de vie et cancer' *platform experts group during cross-cultural translation of the English questionnaires.

Criterion validity: We will check that the translated tools correlate with reference QoL or clinical criteria by calculating correlation coefficients. QLQ-C15 PAL will be treated as the gold standard for QoL tools. A strong correlation between the measures given by the questionnaires and those given by the QLQ-C15 PAL will constitute proof of criterion validity. We will also use the WHO performance status and the performance palliative scale (PPS). These variables will be also dichotomized to calculate the sensitivity and specificity of QoL tools using ROC curves.

Construct validity: This psychometric property will be checked by calculating establishing convergences and differences with the other variables. Factorial analyses as well as Item Response theory methods will be used.

2. Reliability [32-34]: Effect size and the standardized response mean will be computed between each follow-up and then analyzed according to Cohen's classification.

Sensitivity to change:

Internal consistency: we will estimate the strength of the inter-correlations between items, and validate underlying dimensions. We will calculate Cronbach's alpha as an estimator of this internal consistency for each dimension of the QoL questionnaires (at each time assessment). This estimator must be greater than 0.7 to consider a domain homogeneous, but not too close to 1, which would mean that some questions are redundant.

Reproducibility will be studied by calculating ICC using analysis of variance for repeated measurement. An ICC of 0.65 is the minimum required for reproducibility. A Bland and Altman graph will be also done [35,36].

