### Evaluation criteria

#### End of life QoL questionnaires

Within the framework of this study, three questionnaires will be used: QLQ-C15 PAL, QUAL-E, and MVQOLI. The McGill questionnaire was not retained since it assesses the QoL during a short period (quality of life during the 2 days before questionnaire completion).

The EORTC QLQ-C15 PAL reflects patients' QoL during the previous week and investigates two domains (symptoms and physical functioning). An additional item assesses patients' perception of overall QoL. This is a shortened version of the EORTC QLQ-C30, which aims to prevent missing QoL data due to patients' health status. Scores will be calculated using the same algorithm as that used in the QLQ-C30 methodology [22]. Scores will therefore range from 0 (poor QoL) to 100 (best QoL). [23,24].

Taking into account the limited number of dimensions investigated by the EORTC QLQ-C15 PAL, we have selected the QUAL-E and MVQOLI to complement QoL evaluations at the end of life. These two questionnaires dedicated to the end of life have been methodologically validated in their original language, English [25,26].

Twenty-five items and one overall question constitute the QUAL-E questionnaire. Five dimensions can be explored: life completion (particularly through contributions to others), relations with the healthcare system (knowledge and participation of patients in therapeutic decisions), preparation for the end of life, symptom severity (by capturing symptom impact), and affective social support. This questionnaire should be completed during a face-to-face interview. Every question is scored on a 5-point Likert scale [25,26].

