The MVQOLI, developed by Byock *et al*. in 1995 [14,26], includes 15 items in the shortened version and 25 items in the original version. The shortened version was selected since Byock *et al*. previously showed a good correlation (r = 0.93) between these two versions, suggesting that the shortened version does not seem to be associated with a loss of information [14]. This tool explores five dimensions: symptoms (experience of the physical discomfort associated with progressive disease), functional activities (perceived ability to perform usual functions and activities), interpersonal (degree of investment in personal relationships and the perceived quality of one's relations with family and friends), wellbeing (contentment or lack of contentment with self), and transcendence (degree of experienced meaning and purpose in life). It helps professionals to identify factors that affect patient QoL at the end of life. The items related to the 'evaluation' range from -2 to +2, those for the 'satisfaction' range from -4 to +4 and those for 'importance' range from 1 to 5. Each dimension of the questionnaire will be calculated using specific items related to'satisfaction', 'evaluation', and 'importance'.

The score is the sum of the 'evaluation' and 'satisfaction' scores multiplied by the 'importance' score. The total score is obtained by summing each score related to each dimension divided by 10 and then adding 15 points. If the score is negative QoL is poor. The score reflects the impact of each dimension for patients.

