5. To define a period of 'end of life' QoL dimensions that strongly correlate with a patient's health status (physical dimensions, fatigue, pain) should decrease at the end of life, whereas dimensions (psychological, spirituality) more related to the end of life could remain stable and/or could slowly improve. These patterns in longitudinal QoL changes will be captured using mixed model analysis of variance for repeated measurement, and time until definitive QoL score deterioration.

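### Strong correlation with QLQ-C15 PAL is the wrong test for the end-of-life dimensions it does not measure, and the alpha > 0.7 rule suits MVQOLI's weighted scoring poorly

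*Protocol article*

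**What the plan says.** **Criterion validity.** Under Primary objective analyses, "QLQ-C15 PAL will be treated as the gold standard for QoL tools", and "A strong correlation between the measures given by the questionnaires and those given by the QLQ-C15 PAL will constitute proof of criterion validity". No cut-off for strong is given and no pairs of dimensions are named. WHO performance status and the palliative performance scale serve as further criteria. Construct validity is to be examined through convergence with, and difference from, other variables, with factor analysis and item response methods.

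**What the comparator covers.** Under End of life QoL questionnaires, QLQ-C15 PAL "investigates two domains (symptoms and physical functioning"), with one added item on overall QoL. The reason for adding the two new tools begins: "Taking into account the limited number of dimensions investigated by the EORTC QLQ-C15 PAL". The Background says that current tools leave the specific end-of-life dimensions unexplored.

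**Internal consistency.** Under Reliability in the same analysis section, alpha is computed for each dimension at each assessment: "This estimator must be greater than 0.7 to consider a domain homogeneous".

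**MVQOLI scoring.** The short form has 15 items and five dimensions. "Each dimension of the questionnaire will be calculated using specific items related to" satisfaction, evaluation and importance. The score is evaluation plus satisfaction, multiplied by importance.

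**The concern.** An instrument cannot act as gold standard for constructs that, by the article's own account, it does not measure. The stated rule gives no way to read a weak correlation for transcendence, life completion or preparation, although these are the reason for importing the tools. The additional criteria do not fill the gap, because both are measures of functional status.

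Alpha describes the consistency of items that are added together as parallel measures of one thing. The MVQOLI importance item is a multiplier: it amplifies good and bad answers alike, so the scoring formula implies no particular correlation with the other two items. A low alpha could then reflect the scoring structure and not the French wording.

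At stake is the reading of the primary objective. The Discussion says that if psychometric validity is not confirmed, the team may have to consider building a new questionnaire. Low values that come from a difference in construct or from the scoring formula should not count towards that decision.

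**Working it through.** The article states no numerical result on this point, so there is none to reproduce.

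**1. Criterion rule against rationale.**
- Rule: strong correlation with QLQ-C15 PAL proves criterion validity.
- Content of QLQ-C15 PAL: symptoms, physical functioning, one overall item.
- Overlapping content in the new tools: MVQOLI symptoms and function, QUAL-E symptom severity, and the overall measures (MVQOLI total score, QUAL-E overall question).
- Content without a counterpart includes MVQOLI transcendence and QUAL-E life completion and preparation.

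The rule suits the overlapping group and not the last. Illustration, with true correlations and a cut-off of 0.5 all assumed, at the article's n = 338: by Fisher's z, the chance of observing r ≥ 0.5 is 1 − Φ[(atanh 0.5 − atanh ρ) × √335]. This is about 0.00001 for ρ = 0.3 and about 0.01 for ρ = 0.4. With a modest true correlation, a sound dimension would almost never look strongly correlated.

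**2. Three-item alpha for an MVQOLI dimension.** Inputs from the article: 15 / 5 = 3 items per dimension; evaluation −2 to +2, satisfaction −4 to +4, importance 1 to 5. Assumptions: one item of each type per dimension, importance included in alpha, inter-item correlations shown as a range. Let r be the evaluation–satisfaction correlation and c the correlation of importance with each of the other two.

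- Standardized alpha = 3m / (1 + 2m), with m = (r + 2c) / 3. Alpha > 0.7 needs m > 0.7 / (3 − 1.4) = 0.4375, that is r > 1.3125 − 2c.
- Raw alpha = 1.5 × (1 − sum of item variances / variance of the sum). With SDs 1:2:1 (proportional to ranges 4, 8, 4) the variances sum to 6 and the covariances add X = 4r + 6c, so alpha = 1.5X / (6 + X). Alpha > 0.7 needs X > 5.25, that is r > (5.25 − 6c) / 4.

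With c = 0:
- r = 0.6: standardized m = 0.2, alpha = 0.6 / 1.4 = 0.43; raw X = 2.4, alpha = 3.6 / 8.4 = 0.43.
- r = 1.0: standardized m = 1/3, alpha = 1 / (5/3) = 0.60; raw X = 4, alpha = 6 / 10 = 0.60.

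With c = 0.2 and r = 0.6, alpha is 0.60 standardized and 0.56 raw.

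Evaluation–satisfaction correlation needed for alpha > 0.7:

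| c | standardized | raw, SDs 1:2:1 |
|---|---|---|
| 0 | impossible (1.31) | impossible (1.31) |
| 0.2 | 0.91 | impossible (1.01) |
| 0.3 | 0.71 | 0.86 |
| 0.4 | 0.51 | 0.71 |

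The raw ceiling depends on the SDs. With evaluation and satisfaction at 1:2 it rises from 0.60 to 0.667 as the variation in importance shrinks to nothing. It passes 0.7 at c = 0 only in cases such as equal evaluation and satisfaction SDs with an almost constant importance item: 1.5 × (1 − 2/4) = 0.75 at r = 1.

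**3. Two-item alpha (evaluation and satisfaction).** Standardized alpha = 2r / (1 + r): at r = 0.6 it is 1.2 / 1.6 = 0.75, and it passes once r > 0.54. Raw alpha at SDs 1:2 is 8r / (5 + 4r): at r = 0.6 it is 4.8 / 7.4 = 0.65. The version therefore has to be named in advance.

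**The case against.** A reader might infer that the plan would reject the spiritual dimensions, or MVQOLI as a whole, by construction. The documents do not support that, for these reasons:

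- The correlation sentence says what would prove criterion validity. It does not say that a weak correlation disproves it, it has no cut-off, and it is not written per dimension. It can be met by the overlapping dimensions or by overall scores.
- Alpha is listed under Reliability, as the condition for calling a domain homogeneous. It is not a second validity hurdle, and nothing says that one failed dimension rejects a tool. The primary outcome is the ICC, which neither point touches.
- The article does not say that the importance item enters alpha, and it gives no inter-item correlations. The table above contains passes as well as failures.
- Secondary objective 5 says that dimensions "more related to the end of life could remain stable" or slowly improve while physical ones fall. This is a tentative statement about trends over time and does not fix the correlation between patients at one assessment, so it supports the point only weakly.
- Looking for convergence and difference is already planned under construct validity, and the choice of pairs can be left to the SAP.

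All of this stands as a limit on the consequence. It does not remove the defect. The gold-standard sentence is stated outright, the construct-validity sentence does not withdraw it, and alpha is asked of every dimension without exempting weighted scores.

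**Conclusion.** The point holds in a limited form. The criterion-validity rule contradicts the article's own reason for choosing QUAL-E and MVQOLI, as far as the added dimensions are concerned. This part needs no numerical assumption.

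The alpha rule is ill-suited to MVQOLI dimensions. If importance enters alpha and is uncorrelated with the other items, alpha peaks at about 0.60 for SDs of 1:1:1 or 1:2:1. With importance correlating 0.3 to 0.4, alpha passes once evaluation and satisfaction correlate above 0.51 to 0.86, depending on c and the SDs. Failure is likely under some assumptions and not under others. The alpha point concerns MVQOLI's weighted scores only.

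The main risk is misreading low values as a failed translation, not an automatic rejection. The change is worth making before the analysis because it concerns the primary objective and is cheap.

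**What to change.** - Drop the blanket gold-standard wording for QLQ-C15 PAL.
- Prespecify strong correlations, with a cut-off, only where content overlaps: MVQOLI symptoms and function and QUAL-E symptom severity against the QLQ-C15 PAL symptom and physical scores, and overall scores against its overall item.
- Prespecify low correlations for transcendence, life completion and preparation, to be read as discriminant evidence.
- Apply the 0.7 alpha rule to summed scales only.
- For MVQOLI, report standardized alpha on evaluation and satisfaction, and alpha across the five weighted dimension scores for the total. Rely on the ICC for the reliability of the dimension scores.

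Cost: analysis wording. The article says the SAP will be written before the database is locked, so the text can go there. No new data are needed, and the ICC-based sample size (338, or 372 with losses) is unaffected.

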## Methods

### Objectives

Primary objectives are: to cross-culturally adapt the English questionnaires QUAL-E and MVQOLI (Missoula Vitas Quality Of Life Index) and to validate their psychometric properties in the end-of-life setting.

Intermediate objectives are: to translate and adapt the English version of QUAL-E and MVQOLI into French taking into account cultural differences.

Secondary objectives are: to longitudinally assess QoL of cancer patients until death using the QLQ-C15 PAL, the French version of QUAL-E and the Missoula Vitas Quality of Life Index (MVQOLI); to assess the impact of therapeutic strategies on QoL at the end of life; to assess the added value of spontaneous completion of QoL questionnaires to detect a clinically significant change in this setting; to assess the effect of the order of questionnaires on QoL levels; to define a time period for the 'end of life'.

Primary outcomes for cross-cultural and psychometric validation (see also statistical methods): reproducibility of QoL scores estimated by intraclass correlation coefficients; sensitivity to change estimated by effect size and the standard error of mean; discriminant capability; and convergent validity.

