**Collected data and order of administration for QoL questionnaires**				

	**Arms**	**Arms**	**Arms**	**Arms**

Consent	A/B/C/D			

Questionnaires: QLQ-C15, MVQOLI and QUAL-E	A/B/C/D	A/B/C/D	B and D	

Questionnaires: MVQOLI, QLQ-C15 and QUAL-E			A and C	

Questionnaires: MVQOLI, QLQ-C15				D and C

Performance Status, Performance Palliative Scale	A/B/C/D	A/B/C/D	A, B, C, D	

Vital signs, pain (EVA)	A/B/C/D	A/B/C/D	A, B, C, D	

Care (Oncology, Psychology, and so on)	A/B/C/D	A/B/C/D	A, B, C, D	

Responsiveness question	A/B/C/D	A/B/C/D		D and C

^a^D1: First day, the day where the first QoL questionnaires will be completed; D3: 3 days after the first day administration

^b^Can be done D1 at the end of the day if the first was done early in the day

^c^Only MVQOLI and QUAL-E

The above randomization was chosen to explore methodological aspects to optimize QOL tools in the end-of-life setting.

It will allow us to assess the occurrence of an order effect on QoL level by investigating a halo effect and/or a framing effect. Since every patient should complete three questionnaires (MVQOLI, QUAL-E, and the QLQ-C15 PAL), completion of the first questionnaire could influence responses for the following questionnaires, resulting in different QoL levels. Moreover, this effect could be differential depending on the completion order. Since QUAL-E needs a face to face interview, it will be completed by the patient at the end for each arm.

The second randomization will investigate the added value of spontaneous QoL completion to capture clinically important changes in QoL that could have occurred between two planned QoL assessments.

For each allocated group a specific case report form (CRF) will be produced with the corresponding order of QoL questionnaires to prevent changes in completion order (that is, 'cross-over') after the randomization.

Furthermore, the date and time of completion for each QoL questionnaire will be collected. This will allow us to check the order of completion used by the patients.

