### Completion of QoL questionnaire

The QoL questionnaires will be completed before randomization and then every month until death in a time driven design fashion.

Using test-retest methodology, the QLQ-C15 PAL, MVQOLI, and QUAL-E questionnaires will be completed 3 days after the first completion at baseline and before randomization [27].

Though a maximum delay of 15 days is usually allowed between completions to check reproducibility, since these patients have a specific end-of-life profile with sometimes a rapid deterioration in general health status, a maximum delay of 3 days was chosen to minimize the 'risk' of changes in health status.

Since the QUAL-E questionnaire should be completed using a direct interview; patients should complete it last to prevent social desirability bias on QLQ-C15 PAL and MVQOLI evaluations [27].

In order to prevent missing QoL data [28], if a patient is unable to complete questionnaires due to poor health status, QLQ-C15 PAL and MVQOLI could be completed with the help of a proxy (from the medical team) who will have to record the patient's answers without interpretation [29]. A specific item will be completed to take this information into account for the longitudinal analysis of QoL.

All patients will complete QoL questionnaires every month until death.

In arms C and D, depending on patients' health status or perceived QoL, patients will be free to complete the QLQ-C15 PAL and MVQOLI questionnaires (spontaneous QoL completion in an event drive design) between two planned evaluations. A patient CRF including QLQ-C15 PAL and MVQOLI questionnaires, the date of completion, the perception of QoL changes using the Jaescke transition question [30]), and a space for free comments will be created. This booklet will be given to the patients after randomization.

The QoL questionnaires will be administered in a homogeneous way by the same person, a nurse specialized in palliative care, a psychologist, or if necessary a clinical research assistant (CRA), throughout the patient follow-up until death.

Completed questionnaires should be returned to one of the CRAs assigned to the study. In order to deal with holidays, a minimum of two full-time CRAs will be required and identified for each participating center (Table 2).

**Table 2 T2:** Center's participation agreement

Organization	City
Cancer care center Paul Papin	Angers, France

Cancer care center Léon Bérard	Lyon, France

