Cancer care center Georges François Leclerc	Dijon, France

University hospital center Jean Minjoz	Besançon, France

Cancer care center Henri Becquerel	Rouen, France

Hospital center	Cholet, France

Cancer care center Val d'Aurelle-Paul	Montpellier, France

Cancer care institute Bergonié	Bordeaux, France

Cancer care center Oscar Lambret	Lille, France

Cancer care center François Baclesse	Caen, France

Cancer care institute curie	Paris, France

University hospital center	Angers, France

Original CRF and QoL questionnaires will be kept by the Paul Papin Center; while a copy will be kept on site. Postal delivery could be allowed.

If a patient does not want to or cannot complete QoL questionnaires, a note will be made on the unfilled questionnaire with a brief explanation. An item to collect reasons for non-completion should be also completed by CRAs.

Other data will be collected: demographic data, medical history, medical follow-up (social, psychological, pain, cancer treatment), clinical status, and Jaeschke transition question to define minimal clinically important difference for patients in this setting [30].

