### Sample size for secondary objectives

The main endpoint to assess the added value of spontaneous QoL completion is the proportion of patients who report at least one Minimal clinically important difference (MCID) using the Jaeschke transition question.

The minimal clinically important difference is defined as an improvement or a deterioration of 5% in the theoretical QoL score range [23].

With a bilateral alpha type one error of 1% (Bonferroni adjustment for multiple comparisons) a power of 90%, and the following hypotheses:

H0: 70% of patients report an MCID before death in arms A and B

H1: 90% of patients report an MCID before death in arms C and D

It will be necessary to have 243 patients with at least two completed QoL questionnaires between two follow-ups representing 65.4% of the 372 patients included for the primary objective.

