QoL will be described at each follow-up and compared at the inclusion (using Wilcoxon rank test) and then longitudinally analyzed using mixed model analyses of variance for repeated measurement [39-41] to test for the following: a therapeutic strategy effect whatever the follow-up; time effect whatever the therapeutic strategy; interactions between therapeutic strategy and follow-up; and effects of other clinical factors. The best model will be chosen according to the smaller Akaike's information criterion (AIC).

As for the TUDD approach, it will be compared with Log-Rank tests. Univariate and multivariate Cox analyses will be done to compute hazard ratios with 95% CI.

3. To assess the added value of spontaneous QoL completion to detect a clinically significant change in this setting

The proportion of patients who report at least one MCID during follow-up using the Jaeschke transition question will be compared according to the group allocated by randomization using univariate and multivariate logistic regressions.

We will also compute effect size (ES) and standardized response mean (SRM) to explore sensitivity to change according to spontaneous completion of a QoL questionnaire or not. We aim to demonstrate that with spontaneous completion of QoL questionnaires, ES and SRM will be improved.

For the sensitivity analysis, time to definitive QoL deterioration will also be estimated including this spontaneous completion of QoL questionnaires.

Analyses will be performed on an intent-to-treat principle.

4. To assess the effect of questionnaire order on QoL levels Longitudinal QoL analyses will be done as described above QoL will be described at each follow-up and compared at inclusion and then longitudinally analyzed using the mixed model analysis of variance for repeated measurements [39-41]. For the TUDD approach, it will be compared with Log-Rank tests. Univariate and multivariate Cox analyses will be done to compute hazard ratios with 95% CI.

Analyses will be performed on an intent-to-treat principle.

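### Effect size and SRM are planned without an anchor or a split by direction, so a small value does not show an insensitive tool, and a rise with spontaneous forms does not show better sensitivity

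*Protocol article*

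**What the plan says.** The Objectives section of the Protocol article names, among the primary outcomes, "sensitivity to change estimated by effect size and the standard error of mean". Under Primary objective analyses the second index is a different one: "Effect size and the standardized response mean will be computed between each follow-up", with the results then read against Cohen's classification. That sentence names no anchor, change group or direction.

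Elsewhere the article expects change in both directions. Under Sample size for secondary objectives: "The minimal clinically important difference is defined as an improvement or a deterioration of 5% in the theoretical QoL score range". Under objective 5, dimensions tied to health status are expected to fall, while psychological and spiritual ones "could remain stable and/or could slowly improve".

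A possible anchor is collected: the section on completion of the questionnaires lists the "Jaeschke transition question to define minimal clinically important difference for patients in this setting". In Table 1 the row "Responsiveness question" is filled for all arms at D1 and at the retest, and for arms C and D in the notebook column. Its monthly follow-up cell is empty.

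On objective 3, between planned assessments in arms C and D, "patients will be free to complete the QLQ-C15 PAL and MVQOLI questionnaires", according to their health status or perceived quality of life. The analysis text says: "We aim to demonstrate that with spontaneous completion of QoL questionnaires, ES and SRM will be improved". It adds that analyses follow intention to treat.

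**The concern.** Responsiveness means that a score moves when the patient has changed and stays put when the patient has not. An effect size (ES) or standardized response mean (SRM) taken between visits, with no outside statement of who changed, mixes two things: how the patients fared and how well the questionnaire registers it. Where some improve and others decline, the mean change shrinks toward zero however responsive the tool is. Cohen's classes then grade net change in the cohort. The psychological and spiritual dimensions are most exposed, and the Background gives such end-of-life dimensions as a reason for adopting these tools.

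Objective 3 raises a second difficulty. Spontaneous forms are filled in when the patient chooses, prompted by health or perceived quality of life. If they enter the ES and SRM, the forms are partly selected on change, so the index can grow with an unaltered instrument. The stated aim could then be met without any gain in sensitivity.

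**Working it through.** **The plan's own figure.** The article gives no ES or SRM value, target or sample size, so there is nothing to reproduce. The shares and effects below are assumptions that show direction and range.

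**Step 1. Mixed directions, SRM.** Let improvers change by +d, decliners by -d and the rest by 0, with a within-group SD of change of 1. With shares p(i) and p(d):

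- mean change m = d × (p(i) - p(d))
- variance v = 1 + d² × (p(i) + p(d)) - m²
- overall SRM = m / √v

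Take d = 0.8 and 70% of patients changing, so 1 + d² × 0.7 = 1.448.

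| Improve / decline | m | v | Overall SRM |
|---|---|---|---|
| 0% / 70% | -0.56 | 1.134 | -0.53 |
| 10% / 60% | -0.40 | 1.288 | -0.35 |
| 20% / 50% | -0.24 | 1.390 | -0.20 |
| 30% / 40% | -0.08 | 1.442 | -0.07 |
| 35% / 35% | 0.00 | 1.448 | 0.00 |

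Within each changed group the SRM is 0.8 in size in every row. The first row involves no cancellation: the fall to 0.53 comes from the 30% who did not change. The further fall to 0.00 is cancellation.

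**Step 2. The same for ES.** The denominator is the baseline SD, so the overall ES is the change in changed patients × (share worse - share better). At 0.6 SD:

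- 40% worse / 30% better: 0.6 × 0.10 = 0.06
- 50% / 20%: 0.6 × 0.30 = 0.18
- 60% / 10%: 0.6 × 0.50 = 0.30

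**Step 3. Selection by perceived change.** Let perceived change T be standard normal. Let measured change X have mean -0.20, SD 1 and correlation ρ with T. On scheduled forms the SRM is -0.20.

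*Forms filled only when T < -0.5.* The mean of T is then -φ(0.5)/Φ(-0.5) = -0.3521/0.3085 = -1.14, and its variance is 1 + 0.5 × 1.14 - 1.14² = 0.27. So X has mean -0.20 - 1.14ρ and variance 1 - 0.73ρ². At ρ = 0.5 this gives -0.77 / √0.8175 = -0.85.

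*Forms filled when T is beyond 1 in either direction.* The mean of X stays at -0.20 and its SD grows to 1.07, 1.17 and 1.32.

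| ρ | Scheduled | Triggered by decline | Triggered either way |
|---|---|---|---|
| 0.3 | -0.20 | -0.56 | -0.19 |
| 0.5 | -0.20 | -0.85 | -0.17 |
| 0.7 | -0.20 | -1.25 | -0.15 |

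A simulation of 2,000,000 draws gave the same values. At ρ = 0 there is no shift.

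**Step 4. Is an anchor available?** As Table 1 reads, no transition answer accompanies the planned monthly forms. Yet objective 3 compares the proportion reporting an MCID on that question, with 70% assumed in arms A and B, which have no booklet. That endpoint presupposes the question at planned visits, so table and endpoint need reconciling in any case.

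**The case against.** The strongest reply is that the article is silent rather than wrong. It does not say that improvers and decliners are combined, it collects a transition question, and it promises an analysis plan that could stratify by it. This stands as far as it goes: pooling is inferred from the wording. But the method for a listed primary outcome is stated without an anchor, and an analysis plan written before database lock cannot stratify planned visits by an item that was not collected there.

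A reader might infer more than the documents support:

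- *That ES and SRM do not measure sensitivity to change at all.* They are recognised distribution-based indices and are informative where nearly all patients move the same way, as the article expects for physical dimensions, fatigue and pain.
- *That a larger ES with spontaneous forms is guaranteed.* No direction is set for spontaneous completion, and Step 3 shows no rise when both directions trigger a form. Where a rise occurs, its size depends on ρ, that is, on how well the score tracks perceived change.
- *That spontaneous forms will be compared with scheduled forms.* Spontaneous completion is a randomized factor and the analysis is by intention to treat, so a contrast of C+D with A+B is at least as natural. That contrast is unbiased between arms, but if booklet forms enter C and D the index still reflects when forms were filled in.
- *That leaving QUAL-E out of the booklet is an error.* It needs a face-to-face interview, so the omission is deliberate. It only limits the spontaneous-form comparison to MVQOLI and QLQ-C15 PAL.

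It is also fair that ES and SRM are exploratory in objective 3, whose main endpoint is the MCID proportion, and that the sample size rests on reproducibility.

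**Conclusion.** The concern holds in a limited form. As written, ES and SRM for a primary outcome depend on the net mix of change, and a low Cohen class would not show that a French version is unresponsive. Under the assumed mixes, a true within-group SRM of 0.8 (conventionally large) would appear as anything from 0.53 (moderate) to nil. That loss follows from the algebra; its size in this cohort is unknown, since the documents give no shares or effects.

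For objective 3, a rise in ES or SRM that includes spontaneous forms would not by itself demonstrate better sensitivity. The illustrated rise, from 0.20 to between 0.56 and 1.25 in size, rests on a decline-only trigger at -0.5 SD and correlations of 0.3 to 0.7.

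Separately, the standard error of the mean named in Objectives is not a responsiveness index and contradicts the standardized response mean used in both analysis sections. The primary sample size is unaffected. The point should be corrected because it bears on a listed primary outcome and the remedy is cheap.

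**What to change.** 1. Ask the Jaeschke transition question at each planned monthly visit in all four arms, and fill the follow-up cell of Table 1. If the question is already asked there, only the table needs correcting.
2. Report ES and SRM separately for patients who rate themselves worse, unchanged and better. The changed groups should show movement and the unchanged group little. Overall values may stay as description, but should not be graded as evidence of responsiveness.
3. For objective 3, compare the randomized arms (C+D with A+B) at planned visits, or within the same transition category, for MVQOLI and QLQ-C15 PAL. The category is observed after randomization, so a within-category comparison is descriptive. Do not present raw ES or SRM that include spontaneous forms as proof of improved sensitivity, and reword the stated aim to match.
4. In Objectives, replace the standard error of the mean with the standardized response mean.

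The cost is one extra item per planned visit, a case report form change and a few lines in the analysis plan. The Trial status section reports 12 of 372 patients included, so few planned visits would lack the item if the change were made at that stage.
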